### Statistical analysis

SPSS™ 27 and the programming language R are used as software for the statistical analyzes. In the first step at baseline, the data analysis is primarily descriptive according to sample characteristics and outcome measures. Subgroup analyzes between intervention and control group are made using Chi^2^ test, t-test and Mann-Whitney U test, based on the measurement/scales of the related variables. Multilevel regression models will be used to analyze the longitudinal data. This makes it possible to statistically model and control regional differences. Interaction effects are calculated to analyze group differences (intervention vs. control).

If the proportion of missing values (e.g. "don’t know", no answer) is lower than 5%, these will be excluded from the analysis in accordance with the GESIS guidelines [34]. Else, for larger proportions missing data will be imputed using the multivariate imputation by chained equations method [35].

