## Materials and methods

### Design

A non-randomized controlled study (quantitative online survey) over 18 months is ongoing with four measurement points: baseline at the start of the intervention (t0), interim assessments after 6 (t1) and 12 (t2) months, and a final survey after 18 months (t3). In order to be able to identify at least medium effects (Cohen’s d = 0.5) [17] with a test power of 0.80 and an alpha error of 0.05, at least 52 families both from the intervention and control group are required to participate in the study. Since there are hardly any longitudinal intervention studies with particular regional differences in the field of self-help research, the extent of the regional variance (hierarchical data structure) can only be estimated. Assuming 5% intracluster variance explained by the hierarchical data structure, this sample size must be increased by the variance inflation factor [18], resulting in a minimum of 73 families per group. With an estimated drop-out rate of 20–40% based on current studies (e.g. Recapture Life-AYA study [19]), the number of samples ultimately increases to a total of N = 204 families.

The study is conducted with parents and other guardians (all genders and ethnicities) with at least one disabled and/or chronically ill child under 18 years (benefit receipt according to § 37 of Germany’s Social Security Code V and/or level of care > 1), and is limited to the main adult caregivers of the child. The families from the intervention group are recruited via the care service ‘nestwärme gGmbH’ and its network partners in three metropolitan areas of Germany (Trier, Saarbrucken and Munich). The families for the control group are recruited via the umbrella organization ‘Kindernetzwerk e.V.’, which also has regional associations in these regions. In contrast to the control group, which is supported by standard care, the intervention group receives an FGP that carries out a structured assessment in the family and accompanies the family throughout the intervention period. Recruitment for the baseline data collection already started in the intervention areas in January 2022. Control group participants were recruited throughout Germany, with 102 families consenting to take part in the study until the end of September 2022.

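### Region is the only clustering the plan names, although the intervention is delivered by Family Health Partners in one arm only; if they serve several families each, the standard error of the intervention effect may be too small

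*Protocol article*

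**What the plan says.** The Design section contrasts the arms: controls have standard care, whereas "the intervention group receives an FGP that carries out a structured assessment in the family and accompanies the family throughout the intervention period". The same section identifies the hierarchy with region, remarking that "the extent of the regional variance (hierarchical data structure) can only be estimated". The inflation of the sample size rests on this: "Assuming 5% intracluster variance explained by the hierarchical data structure", the figure of 52 families per group is raised, "resulting in a minimum of 73 families per group".

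The Statistical analysis section gives the longitudinal model the same single clustering purpose: "Multilevel regression models will be used to analyze the longitudinal data. This makes it possible to statistically model and control regional differences". Group differences are to be read from interaction effects.

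Neither section names the FGP as a level or cluster. The number of FGPs and their caseloads are not given. The Measurements section shows only that there is more than one FGP, since all of them are to be interviewed for the process evaluation.

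**The concern.** The FGP assesses the family's needs, counsels and coordinates, and opens access to regional services. FGPs will plausibly differ in skill and contacts, so families with the same FGP may have correlated outcomes. Control families have no counterpart. This is a partially nested design: clustered in one arm, independent families in the other.

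A region effect does not stand in for this. It does not separate FGPs working in the same region, and it applies the same structure to controls, who were recruited throughout Germany and have no FGP. The FGP component would then be counted largely as independent family-level noise. The standard error of the group effect would be too small, the confidence interval too narrow, and the type I error above the stated 0.05. This matters for use of the result, because the Discussion expects the findings to be carried into standard care, where other FGPs would deliver the service.

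**Working it through.** **1. The plan's own figures.** Inputs from the Design section: standardized difference 0.5, "with a test power of 0.80 and an alpha error of 0.05", 52 families per group, ICC 0.05, 73 per group after inflation, 204 in total.

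- n per group = 2 × (z_alpha + z_beta)² / 0.5² gives 50 one-sided (t-test 51) and 63 two-sided (t-test 64). Sidedness is not stated; 52 is close only to the one-sided result.
- Design effect: 73 / 52 = 1.404. From 1 + (m − 1) × 0.05 = 1.404, m is about 9.1. With m = 9, 52 × 1.4 = 72.8, which rounds up to 73. The cluster size of 9 is not stated, and it does not match three intervention regions (73 / 3 = 24 to 102 / 3 = 34 families each).
- Drop-out: 1 − 73 / 102 = 28.4%, inside the stated 20–40%.

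The chain 52 → 73 → 102 per group can be followed, and its only clustering term is attributed to region.

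**2. Closed form for clustering in one arm.** With m families per FGP, the intervention-arm variance is inflated by DE = 1 + (m − 1) × ICC, and the control arm by 1. With equal arms, true SE / naive SE = sqrt((DE + 1) / 2), and the two-sided type I error is 2 × (1 − Phi(1.96 / that ratio)). Number of FGPs and FGP ICC are assumed. At 102 per arm and ICC 0.05:

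- 6 FGPs: m = 17, DE = 1 + 16 × 0.05 = 1.80, ratio = sqrt(1.40) = 1.18, type I error 0.098.
- 12 FGPs: m = 8.5, DE = 1 + 7.5 × 0.05 = 1.375, ratio = sqrt(1.1875) = 1.09, type I error 0.072.

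This compares with an analysis that has no region term, so it does not quite describe the plan.

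**3. Simulation with a region intercept.** Data with no true effect, 102 families per arm, one outcome per family, no true regional variance, intervention FGPs spread over 3 regions, controls over an assumed 10 regions that include those 3. The model was fitted by REML with a random intercept for region only and tested against 1.96; 3,000 runs per setting.

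| FGPs | FGP ICC | Rejection at nominal 0.05 | Empirical SD / mean model SE |
|---|---|---|---|
| 6 | 0 | 0.047 | 0.97 |
| 6 | 0.02 | 0.061 | 1.06 |
| 6 | 0.05 | 0.085 | 1.15 |
| 6 | 0.10 | 0.140 | 1.29 |
| 12 | 0 | 0.048 | 0.99 |
| 12 | 0.02 | 0.052 | 1.00 |
| 12 | 0.05 | 0.069 | 1.08 |
| 12 | 0.10 | 0.085 | 1.13 |

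The Monte Carlo standard error near 0.05 is sqrt(0.05 × 0.95 / 3000) = 0.004, so 0.052 is indistinguishable from nominal. The ICC 0 rows show that the excess comes from the FGP component. The region intercept absorbs only a little of it: at ICC 0.05 the rejection rate falls from 0.098 to 0.085 (6 FGPs) and from 0.072 to 0.069 (12 FGPs).

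**The case against.** **The random effects are not listed.** The Statistical analysis section describes what multilevel models make possible; it does not say that region is the only level, and a fuller plan that is not shown may add the FGP. This stands as a caution. It does not remove the point, because the Design section itself equates the hierarchical structure with regional variance and the analysis section repeats that purpose. The source of clustering is stated, and the provider is left out of it.

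**Sharing of FGPs is nowhere stated.** True; it is an inference, though a strong one. One FGP per family would need about 102 of them, all to be interviewed qualitatively, while the limitations paragraph of the Discussion describes affected families, qualified professionals or both as few.

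**The size rests on assumptions.** Also true. The ICC of 0.05 is the protocol's guess for region, borrowed here for FGPs. A reader might take the far end of the closed form, a type I error of 0.147 or 0.229 with 34 families per FGP at ICC 0.05 or 0.10, as the likely size. The documents do not support that: 102 / 34 = 3 means about one FGP per region, where FGP and region coincide among intervention families, and the formula ignores the region term.

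**Power.** A reader might infer that the trial is underpowered for the same reason. That does not follow. The plan already inflates both arms by about 1.4. At m = 9 and ICC 0.05, FGP clustering needs an average of (1.4 + 1) / 2 = 1.2; at m = 17 it needs (1.8 + 1) / 2 = 1.4. The allowance may cover FGP clustering if regional variance is small.

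**Conclusion.** The point holds in conditional form and concerns the analysis more than the sample size. Region is the only clustering the article names, while the treatment is delivered by providers who exist in one arm. If FGPs serve several families and outcomes correlate within FGP, a region-only model understates the standard error of the intervention effect. For 6 to 12 FGPs and an ICC of 0.05, the understatement is about 7% (1 − 1/1.08) to 13% (1 − 1/1.15). Over ICCs of 0.02 to 0.10, the consequence runs from negligible to a type I error of 0.14.

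These figures assume the number of FGPs, the ICC, the spread of controls over regions and a single outcome per family; none is given in the article for this purpose. It would go too far to say that the standard errors are too small as a matter of fact, or that the result cannot apply beyond the FGPs employed. The first depends on unstated quantities, and the second on whether FGPs are treated as a sample from a wider pool.

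**What to change.** - Record for every intervention family which FGP accompanies it.
- Add a random FGP effect in the intervention arm only, with each control family as its own unit (a partially nested model), and use Satterthwaite or Kenward-Roger degrees of freedom.
- Keep region as a fixed covariate if region and FGP cannot both be estimated as random.
- Report the number of FGPs, their caseloads and the estimated FGP ICC.
- State in the sample-size paragraph that the inflation from 52 to 73 was derived for regional clustering only.

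The cost is one identifier per intervention family, which the article does not say is already held, and a few sentences in the analysis plan. Confidence intervals will be wider if the FGP variance is not negligible. With few FGPs the price can be substantial: 6 FGPs leave at most 6 − 1 = 5 degrees of freedom for the FGP variance. If that variance proves close to zero, less is lost. The article describes the study as ongoing, and 18 months from the end of control recruitment in September 2022 falls after its publication in July 2023, so at publication the change could still be made before the final data were complete.

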### Ethics, registration and dissemination

This study was approved by the Local Psychological Ethics Committee at the University Medical Center Hamburg-Eppendorf (authorization number: LPEK-0370). The study was prospectively registered on the German Clinical Trials Register before the enrolment of participants started (ID: DRKS00027465, 4 January 2022), and retrospectively on ClinicalTrials.gov (ID: NCT05418205, 14 June 2022). The authors confirm that all ongoing and related trials for this intervention are registered.

At the beginning of the study, all attendees gave written informed consent on the study and agreed to participate in the baseline and follow-up surveys after 6, 12 and 18 months. The privacy of the participants is guaranteed by storing encrypted data. Every participant will receive a pseudo-anonymous study number. The key is only accessible to the study team and co-workers. Data and material will only be used in coded form within possible collaboration projects.

The results of this study will be made available through peer-reviewed scientific journals and presentations at relevant conferences. Furthermore, a project website was launched to provide information about the current status of the project (https://forschungsprojekt-nest.de/). A handbook with recommendations for the cross-project implementation of sustainable processes and structures for the needs-based care (with special regional consideration, cost and service provider-specific implementation barriers and legal regulation needs) will be developed.

## Discussion

The presentation and analysis of general and/or specific mechanisms of action of a regionally networked organization that operates across sectors, costs and service providers with regard to their effectiveness for families with children in need of care is new. As far as can be seen, only the case management in the German PariSozial project [36] has been subject to a scientific evaluation–albeit under the premise of its effectiveness with regard to ensuring the need for care. The question of the effectiveness of the support networks in relation to multidimensional outcomes has not yet been consistently posed nor answered. Here, multidimensional outcomes include access to care, family health and quality of life, preservation and mobilization of self-help resources and service provider-financed care.

The strength of this study is that it, besides the usual variables of ‘prescribed’ care, looks at the health and resilience of all family members involved by examining how a FGP can influence the entire family system with regard to increasing quality of life, resilience and self-efficacy. The network structures of FGP also open up better to previously unknown regional supply offers (incl. youth welfare office, school, social pediatric centers etc.). In addition, the comprehensive information collected in this study will also enable us to answer other research questions regarding families with children in need of care, such as relationships between individual needs and existing range of services. Therefore, a structured assessment (family-reported needs) is to be developed as well as a handbook (transfer model) with recommendations for the implementation of sustainable processes and structures for the needs of families with children in need of care. Eventually, these results will be applied in the standard care to strengthen and relieve families with disabled or chronically ill children.

There are, however, a number of limitations. A possible limitation of this study is that we only use self-reported outcomes for the impact analysis of FGPs as our primary research goal. Outcomes reported by someone else (e.g. clinical data) are not planned. However, for the most part we use psychometrically tested instruments developed for different contexts and languages (incl. German). Compared to other studies using the measurements, we expect a slightly higher proportion of missing values in some items after 18 months, but tackling this issue with imputation techniques is feasible. Missing values in psychometric testing are not a problem per se, but may result in biased reliability scores [37]. Finally, the number of cases in this project is limited overall because the number of affected families and/or qualified professionals is comparatively small; not every affected family needs an FGP per se, and the offer is not sufficiently known.
